### Sample size {14}

Based on data from community-dwelling frail older adults, it is estimated that CGA will improve the GAS score by at least 10 points from an average score of 36 at baseline (which presents a change in one standard deviation, equivalent to a medium effect size) [25].

It is estimated that a cluster randomised trial with an average cluster size of 20 participants (coefficient of variation of sizes = 1) would require 16 hospital sites (clusters) with 8 sites in the intervention and control arm, respectively, to achieve 90% power to detect a mean difference in GAS score of 10 units at 3 months follow-up. This power calculation, giving a sample size of 320, assumes a common standard deviation of 10 units and an intra-cluster correlation coefficient of 0.3. To achieve sufficient power for the analysis of the secondary outcome of GAS at 12 months, an allowance for a 33% loss to follow-up over the 12 months was included, requiring baseline GAS observations from 478 participants. The 16 sites will be expected to each have a minimum of 55 patients who meet the eligibility criteria. Based on previous studies, it is estimated that approximately 10% of eligible patients will not consent to participate [26, 29] and a further 35% will not meet the frailty criteria [38] leaving a recruitment target of 500 (approximately 30 at each site). Assumptions in the sample size calculation will be re-estimated on trial data at the mid-point of the planned recruitment period.

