## Statistical methods

### Statistical methods for primary and secondary outcomes {20a}

Data will be analysed at the individual patient level. The primary outcome, Goal Attainment Scaling (GAS) scores at three months, will be analysed using a linear regression model with the intervention group as a binary covariate and baseline GAS score as a continuous covariate. To allow for the clustering of data within study centres, inference will be based on robust standard errors. Multiple imputation will be used if there is more than 5% missing data on the three-month GAS scores. Subgroup analysis of GAS scores at three months will be undertaken based on baseline characteristics of patients (including age, CKD stage, and frailty status) and study site (including unit size). Subgroup effects will be assessed via treatment-by-subgroup interactions in linear regression models.

Repeatedly measured continuous secondary outcomes (GAS scores at 6 and 12 months, EQ-5D-5L scores, FI) will be analysed using mixed models for repeated measures (MMRM) with a random intercept for the study centres and an unstructured variance–covariance matrix to model the within-patient correlation structure due to the repeated measurements. The models will have fixed effects for the intervention group, categorical time, the intervention-by-time interaction, and baseline measurements of the outcome. The primary results will be the treatment effect estimates at 6 and 12 months and 95% confidence limits.

Other secondary outcomes will be analysed using regression models appropriate for the type of outcome. The effect of CGA on the rate of hospital admission will be tested using a Poisson regression model with a random intercept for study centres and the effect of CGA on time to all-cause mortality and time to hospital admission will be assessed using Cox regression with frailty (random intercepts) for study centres. A detailed statistical analysis plan will be made public before unblinding of the trial statistician and other study personnel at the coordinating centre.

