### Methods for additional analyses (e.g. subgroup analyses) {20b}

Subgroup analysis may be undertaken based on participant (age, CKD stage, frailty) and study site (region, size) characteristics where possible.

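### The arm-by-subgroup interactions for age, CKD stage and frailty are tested without a hospital term, which gives up precision that a within-hospital estimate would recover

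*Protocol article*

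**What the plan says.** In the protocol article, the section on statistical methods for primary and secondary outcomes {20a} analyses 3-month GAS by linear regression on arm and baseline GAS. Clustering is handled through robust standard errors only. The same paragraph continues: "Subgroup analysis of GAS scores at three months will be undertaken based on baseline characteristics of patients (including age, CKD stage, and frailty status"), together with site characteristics such as unit size, and then "Subgroup effects will be assessed via treatment-by-subgroup interactions in linear regression models".

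The following paragraphs of {20a} do name centre terms: a random intercept in the repeated-measures and Poisson models, and a frailty term in the Cox model. The 3-month GAS paragraph names none.

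Section {20b} returns to the topic in softer terms and gives no model: "Subgroup analysis may be undertaken based on participant (age, CKD stage, frailty) and study site (region, size) characteristics where possible".

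The sample size section {14} "assumes a common standard deviation of 10 units and an intra-cluster correlation coefficient of 0.3". No power or precision is stated for any interaction.

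**The concern.** Unit size and region are properties of the hospital, so their interaction with arm can only be estimated between hospitals. Age, CKD stage and frailty differ between patients of the same hospital. Their interaction with arm is the difference, between arms, of a contrast that can be formed inside each hospital, where the hospital's own GAS level cancels.

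A regression without a hospital term does not use that cancellation. On the plan's assumption, 30% of the GAS variance lies between hospitals, and this part stays in the error of the interaction. Robust standard errors describe the extra noise but do not remove it. The estimate also blends two questions: whether CGA works differently for different patients within a hospital, and whether it works differently in hospitals that see more of one kind of patient.

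At stake is how well the trial can say which patients benefit, and how cleanly that answer refers to patients and not to hospitals.

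**Working it through.** **Inputs from the sample size section {14}.** The design "would require 16 hospital sites (clusters) with 8 sites in the intervention and control arm, respectively", with an "average cluster size of 20 participants (coefficient of variation of sizes = 1"), an SD of 10 and an ICC of 0.3. The total variance of 100 therefore splits into 30 between and 70 within hospitals, for 320 analysed patients.

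**The plan's own figure.** The stated aim is "to achieve 90% power to detect a mean difference in GAS score of 10 units at 3 months follow-up". With efficient weighting of unequal clusters:
- L = 20×0.3/(20×0.3 + 0.7) = 0.896
- design effect = (1 + 19×0.3)/(1 − 1²×0.896×0.104) = 6.7/0.906 = 7.39
- standard error = √(2×100×7.39/160) = 3.04
- power = Φ(10/3.04 − 1.96) = 0.908 (two-sided 5% and a normal reference assumed)

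The 90% is reproduced on this basis, so the 30/70 split is the plan's own.

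**Assumptions added here.** A binary patient-level subgroup with 50% prevalence, whose share varies between hospitals with ICC r. The documents give neither figure, so r is shown from 0 to 0.2. Baseline GAS is left out of both models.

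**Hand approximation, equal clusters of 20, 8 hospitals per arm.**

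With hospital terms, the within-hospital sum of squares of the subgroup variable is 8×19×0.25×(1 − r) = 38(1 − r) per arm, so the variance is 2×70/[38(1 − r)].
- r = 0: 140/38 = 3.68, SD 1.92
- r = 0.2: 140/30.4 = 4.61, SD 2.15

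Without hospital terms, the variance is about 2×[70/40 + 30×8×V/40²]. Here V = 5(1 + 19r)×7/8 is the variance of a hospital's subgroup total about the arm mean.
- r = 0: V = 4.375, variance 2×(1.75 + 0.656) = 4.81, SD 2.19
- r = 0.2: V = 21, variance 2×(1.75 + 3.15) = 9.80, SD 3.13

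The variance ratios are 4.81/3.68 = 1.31 and 9.80/4.61 = 2.13. Simulation with equal clusters gave SDs of 2.17 against 1.89 at r = 0 and 3.17 against 2.12 at r = 0.2 (ratios 1.33 and 2.24).

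**Simulation with the plan's unequal clusters (CV 1).** SD of the interaction estimate in GAS points:

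| Subgroup ICC (assumed) | No hospital term | Hospital indicators | Variance ratio |
|---|---|---|---|
| 0 | 2.34 | 2.04 | 1.32 |
| 0.05 | 2.63 | 2.13 | 1.52 |
| 0.10 | 2.81 | 2.15 | 1.71 |
| 0.20 | 3.43 | 2.33 | 2.17 |

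Repeat runs with other random draws gave ratios of 1.28 to 1.32 at ICC 0 and 2.17 to 2.48 at ICC 0.2. In one of these runs a random centre intercept gave nearly the same SDs as hospital indicators (2.01 to 2.25 against 2.03 to 2.30 at ICC 0 and 0.2).

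**If the subgroup contrast itself varies between hospitals.** At an assumed SD of 3 points for that variation, the SDs were 3.38 without and 3.00 with hospital indicators, a variance ratio of (3.38/3.00)² = 1.27. At an assumed SD of 5 points and subgroup ICC 0.05, they were 4.38 against 4.13, a ratio of 1.12.

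**Bias.** With no true interaction, and case-mix related only to the hospital's GAS level, the model without hospital terms averaged 0.03 points, which is no bias. When the CGA effect was made to vary with case-mix (assumed 3 points per SD of subgroup share), it averaged 1.04 points at subgroup ICC 0.05 and 1.52 at 0.10. Hospital indicators averaged 0.01 and −0.05, and a random intercept 0.14 and 0.16.

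**The case against.** **The model is not fully spelled out.** The article does not say in words that hospital terms are excluded from the subgroup models, and the promised analysis plan could add them. This stands as a limit. But the paragraph describes a linear regression with robust standard errors, and the same section names centre terms wherever other models use them. Read as written, the subgroup model has none.

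**The analyses are secondary.** Section {20b} makes them optional, and nothing is powered for them. This bears on the weight of the point, not on its correctness.

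**A reader might infer that omitting hospital terms inflates the false-positive rate and that adding them restores 5%.** The figures do not support this. Without hospital terms, uncorrected robust standard errors and a normal cut-off (which the article does not state) rejected a true null in 10.0–14.6% of simulated trials. Hospital indicators with the same standard error and cut-off still rejected in 10.1–11.7%. Most of the excess comes from uncorrected robust standard errors with 16 unequal clusters, which hospital terms do not cure. Model-based standard errors with hospital indicators hold about 5% only if the subgroup contrast is identical in every hospital. If it varies with an assumed SD of 3 to 5 points, they reject in 17–31%.

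**A reader might also infer that the plan will produce false subgroup effects.** It does so systematically only if the CGA effect varies with hospital case-mix. The study setting section {9} foresees both tertiary and peripheral sites, so differing case-mix is plausible, but no document says that the effect follows it or by how much.

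**Conclusion.** The point holds as a loss of precision in the patient-level subgroup interactions. On the plan's SD, ICC and cluster sizes, leaving out the hospital term raises the variance about 1.3 times with identical case-mix and up to about 2.2 times at an assumed subgroup ICC of 0.2. The penalty shrinks if the subgroup contrast differs between hospitals (3.38 against 3.00 points at an assumed SD of 3).

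The mixing of between- and within-hospital contrasts is real, but it becomes bias only under effect variation that follows case-mix. No size can be put on that from the documents. No claim about type I error belongs to this point.

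The result rests on 50% prevalence, the assumed subgroup ICCs, the omission of baseline GAS and 320 analysed patients. It does not touch unit size, region or the primary analysis. It is a worthwhile, inexpensive improvement to secondary analyses and does not threaten the trial's main conclusion.

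**What to change.** For age, CKD stage and frailty, regress 3-month GAS on hospital indicators, baseline GAS, the subgroup variable and the arm-by-subgroup product, and report that product as the subgroup test. The indicators absorb the arm main effect. A random centre intercept is an acceptable alternative with nearly the same precision, though it left about 0.15 points of bias in the case-mix setting above.

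Name the standard error in the same sentence: cluster-robust with a small-sample correction, for example CR2 with a t reference and Satterthwaite degrees of freedom. The model-based standard error should not be used, for the reason given under the objections. A t reference alone is not enough: with hospital indicators, ordinary robust standard errors and 15 degrees of freedom, the null rejection rate was still 8.6–10.4% at CV 1. The CR2 version was not itself simulated here.

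Keep the planned model for unit size and region, and for displaying the effect within each subgroup. Leave the primary analysis unchanged.

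The cost is one sentence in the analysis plan before unblinding, with no new data. The downside is that a hospital whose participants all fall in one subgroup category adds nothing to that interaction.

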**Secondary objectives**		
To determine whether CGA improves attainments of patients’ own goals of care over time	GAS	Baseline, 3, 6 and 12 months
To determine whether CGA improves patient’s quality of life over time	EQ-5D-5L	Baseline, 3, 6 and 12 months
To determine whether CGA favourably affects the trajectory of frailty status over time	FI	Baseline, 3, 6 and 12 months
To determine whether CGA reduces mortality during the 12-month follow-up	All-cause mortality (time to event, proportion) Cause-specific mortality (time to event and proportion)	Continuous
To determine whether CGA reduces the number of hospital admissions during the 12-month follow-up	Hospital admissions (number and reason)	Continuous
To determine whether CGA reduces the hospital length of stay number during the 12-month follow-up	Hospital length of stay (days)	Continuous
To determine whether CGA reduces admissions to RACF at 12 months follow-up	Time to RACF admission	Continuous
To determine whether CGA is cost-effective within the trial context	Health care use analysis	Continuous

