### Methods in analysis to handle protocol non-adherence and any statistical methods to handle missing data {20c}

Protocol deviations (e.g. delayed CGA, cross-over) will be investigated in sensitivity analyses. Imputation of randomly missing values will be tested during sensitivity analyses.

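### The repeated-measures model names GAS at 6 and 12 months only, although Table 2 also lists 3 months; the 3-month score should be stated as part of the response

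*Protocol article*

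**What the plan says.** All places are in the protocol article.

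- **Statistical methods {20a}, response:** "Repeatedly measured continuous secondary outcomes (GAS scores at 6 and 12 months, EQ-5D-5L scores, FI) will be analysed using mixed models". Of the three outcomes in that bracket, only GAS carries visit times.
- **Same section, covariance:** a random intercept for study centre and "an unstructured variance–covariance matrix to model the within-patient correlation structure due to the repeated measurements".
- **Same section, fixed effects:** "The models will have fixed effects for the intervention group, categorical time, the intervention-by-time interaction, and baseline measurements of the outcome".
- **Same section, what is reported:** "The primary results will be the treatment effect estimates at 6 and 12 months and 95% confidence limits".
- **Outcomes {12}, Table 2:** GAS over time, EQ-5D-5L and FI all have the same entry, "Baseline, 3, 6 and 12 months".
- **Sample size {14}:** to power the secondary GAS outcome at 12 months, "an allowance for a 33% loss to follow-up over the 12 months was included", which raises the number needed at baseline from 320 to 478.
- **Missing data:** for the primary analysis, "Multiple imputation will be used if there is more than 5% missing data on the three-month GAS scores". Section {20c} adds "Imputation of randomly missing values will be tested during sensitivity analyses". Under {18b}, nothing is collected after a participant withdraws.

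**The concern.** A mixed model for repeated measures handles dropout under missing-at-random only if the observed outcomes that drive dropout are in the model. For a participant lost between 3 and 6 months, the last relevant observation is the 3-month GAS. If that score is not in the response, the participant has no GAS outcome at all in the model and drops out of it. The adjustment that the model is meant to provide is then lost for that group.

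This matters here for three reasons. Recruitment was enlarged specifically to support GAS at 12 months. The plan itself expects a third of participants to be lost by then. And participants and clinicians know the allocation, so a link between early goal attainment and staying in the trial is plausible and need not be the same in both arms. The multiple-imputation rule covers only the 3-month score, and the sensitivity imputation in {20c} does not say whether it covers the later visits or uses the 3-month score.

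**Working it through.** **1. The plan's own figures.** Inputs from {14}: 16 clusters of mean size 20 (coefficient of variation 1), SD 10, ICC 0.3, difference 10. A two-sided 5% level is assumed.

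- L = 20 / (20 + 0.7/0.3) = 0.896
- Design effect with the relative-efficiency correction for unequal clusters = (1 + 19 × 0.3) / (1 − 1² × 0.896 × 0.104) = 6.7 / 0.906 = 7.39
- Effective n per arm = 160 / 7.39 = 21.6; SE = 10 × √(2/21.6) = 3.04
- Power = Φ(10/3.04 − 1.96) = Φ(1.33) = 0.91, matching the stated 90%
- 320 / 0.67 = 477.6, so 478, as stated

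The SE of about 3.0 is the yardstick below.

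**2. Who is affected.** Only participants lost between 3 and 6 months. Those lost earlier have no follow-up GAS in either version, and those lost later still contribute their 6-month score. The plan gives no timing.

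- Even monthly loss: 0.67^(3/12) − 0.67^(6/12) = 0.905 − 0.819 = 0.086, or about 41 of 478.
- The front-loaded schedule used in step 3: 20%, or about 96 of 478.

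**3. Large-sample simulation.** Maximum likelihood, unstructured covariance, 30,000 per arm, no cluster effect. Assumptions, none of them in the protocol: true effect 10 at every visit, SD 10, baseline SD 5, adjacent-visit correlation r of 0.5 or 0.8, about 20% lost by month 6 and 33% by month 12, and a dropout logit changing by 1 per 10 GAS units. Estimates are month 6 / month 12, with one common baseline slope.

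| Dropout rule | r 0.5, 6/12 only | r 0.5, 3/6/12 | r 0.8, 6/12 only | r 0.8, 3/6/12 |
|---|---|---|---|---|
| Completely random | 10.07 / 10.17 | 10.06 / 10.16 | 9.87 / 9.85 | 9.94 / 9.91 |
| On baseline only | 10.04 / 10.11 | 10.03 / 10.11 | 10.01 / 10.02 | 10.01 / 10.02 |
| Low scorers leave, both arms | 9.44 / 9.55 | 10.01 / 9.85 | 9.28 / 9.42 | 10.10 / 10.09 |
| High scorers leave, both arms | 9.51 / 9.90 | 10.05 / 10.19 | 9.17 / 9.36 | 10.05 / 10.07 |
| Low scorers leave, intervention only | 10.88 / 10.36 | 10.02 / 9.91 | 11.33 / 10.90 | 9.99 / 9.81 |
| Low scorers leave, control only | 9.30 / 9.92 | 10.12 / 10.36 | 8.87 / 9.05 | 10.14 / 10.09 |
| Low leave intervention, high leave control | 11.69 / 10.77 | 10.05 / 9.90 | 12.55 / 12.09 | 9.89 / 9.93 |
| High leave intervention, low leave control | 8.36 / 9.06 | 10.01 / 9.93 | 7.34 / 7.79 | 10.02 / 10.00 |

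Simulation error is about 0.1. The one value well off 10 with the 3-month score included (10.36) is simulation noise: larger runs put the 3/6/12 model at about 9.9 to 10.1 whenever dropout depends on the last score.

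With a true effect of 0 and r 0.8, a shared low-score rule gives −0.04 / −0.04 from the 6/12-only model. Low scorers leaving intervention and high scorers leaving control give 2.66 / 2.11, against −0.07 / −0.12 with the 3-month score included.

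**4. Milder timing.** With even loss over 12 months, a shared rule, exchangeable correlation 0.5 to 0.7 including baseline, and dropout odds changing 1.6- to 2.7-fold per SD, the 6/12-only model gives 9.84 to 9.97 at month 6 and 9.85 to 10.00 at month 12.

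**5. Against the SE.** Largest shared-rule bias: 10 − 9.17 = 0.83, and 0.83 / 3.04 = 0.27 SE. Largest bias with differing rules: 10 − 7.34 = 2.66, and 2.66 / 3.04 = 0.88 SE.

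**6. Baseline slope.** Letting the slope vary by visit moved the 6/12-only estimates by about 0.05, even with true slopes of 1.2, 0.6 and 0, and the 3/6/12 estimates by at most about 0.15.

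**The case against.** The strongest reply is that nothing is excluded. The section has just assigned 3-month GAS to the primary analysis, so the bracket may only be naming which outcomes are secondary. EQ-5D-5L and FI share the model with no visit restriction, Table 2 includes 3 months, and no sentence says the 3-month score is left out. The protocol also promises a detailed analysis plan, where the visits in the model would normally be listed. This reading is fair and may be what is intended. But a separate sentence already fixes 6 and 12 months as the reported contrasts, so on this reading the limit placed on GAS alone does no work. The stated model text and Table 2 do not match as they stand.

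The second reply is that the bias is small. Under a rule shared by both arms that stands: at most about a quarter of a standard error, and near zero if loss is spread evenly. It does not carry over to rules that differ by arm.

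Two stronger readings are tempting and are not supported. A reader might infer that the 6- and 12-month effects are biased towards zero. The protocol gives no dropout mechanism, and the direction reverses when low scorers leave mainly the intervention arm or high scorers mainly control. A reader might also infer that the single baseline slope distorts the effects, but step 6 of the working shows no material change.

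**Conclusion.** The point holds as a mismatch between the model text and Table 2 with a conditional consequence. Read literally, participants lost between 3 and 6 months are absent from the GAS model, and dropout driven by the 3-month score is not handled.

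For a true effect of 10 units:

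- no bias if dropout is random or depends only on baseline;
- attenuation of about 0 to 0.8 units if both arms share one score-dependent rule;
- bias of up to about 2.7 units, in either direction, if the rule differs by arm.

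These sizes rest on assumed correlations, dropout strength and dropout timing. Including the 3-month score removes the bias where dropout depends on observed scores; it would not cure dropout that depends on unobserved ones. The primary 3-month analysis is untouched. This is a free improvement to a secondary analysis, not a flaw that threatens the trial's main conclusion.

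**What to change.** In {20a} and in the analysis plan, state that the GAS response vector for the repeated-measures model contains the 3-, 6- and 12-month scores, in line with Table 2. Keep the 6- and 12-month contrasts as the reported GAS results and leave the primary 3-month regression as it is. A baseline-by-time term is optional.

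The cost is one sentence. The 3-month scores are already collected, and the only addition to the model is the time, interaction and covariance parameters for one more visit. The protocol says that the analysis plan will be made public before unblinding, so the change can be made there.

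### The repeated-measures model gives each hospital one intercept held constant over visits; if hospital effects vary between visits, standard errors are mildly too small at 6 and 12 months and severely too small for any between-visit contrast

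*Protocol article*

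**What the plan says.** Statistical methods {20a} analyses the repeatedly measured secondary outcomes with "mixed models for repeated measures (MMRM) with a random intercept for the study centres and an unstructured" covariance matrix. The purpose given for that matrix is "to model the within-patient correlation structure due to the repeated measurements". The model has "fixed effects for the intervention group, categorical time, the intervention-by-time interaction, and baseline measurements of the outcome". The results named from it are these: "The primary results will be the treatment effect estimates at 6 and 12 months and 95% confidence limits".

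No centre-by-visit term is stated. Robust standard errors are stated only for the 3-month primary analysis.

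Table 2 in Outcomes {12} sets secondary objectives about change over time for GAS, EQ-5D-5L and frailty, for example "To determine whether CGA favourably affects the trajectory of frailty status over time". Sample size {14} "assumes a common standard deviation of 10 units and an intra-cluster correlation coefficient of 0.3", with 16 hospitals, 8 per arm. It does not say how strongly a hospital's effect at one visit correlates with its effect at another.

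**The concern.** The patient level is modelled freely over visits, but the hospital level is not. One intercept per hospital means that a hospital's deviation is the same at every visit. The unstructured matrix sits within patients, so it cannot represent a shift shared by all patients of one hospital at one visit. The model treats any such shift as independent patient noise that averages out over the hospital's patients.

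This affects two kinds of result differently. At a single visit the constant intercept still carries most of the hospital variance, so the loss is partial. In a contrast between two visits the constant intercept cancels, and the contrast is assessed almost as if individual patients had been randomised. A claim that CGA changes a trajectory could then rest on hospital-level drift.

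Hospital-by-visit variation is possible here. Site nurses or delegates administer GAS, EQ-5D-5L and the FI (section {18a}), clinicians and participants are unblinded ({17a}), and what follows a CGA depends on local services or the GP ({11a}).

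**Working it through.** **Inputs.** From Sample size {14}: 16 hospitals (8 per arm), "an average cluster size of 20 participants (coefficient of variation of sizes = 1"), SD 10, ICC 0.3. From Table 2: visits at 3, 6 and 12 months. Assumed: two-sided 5% (inferred from the 95% limits); between-visit correlation of hospital effects *r* from 0.5 to 1; within-patient residual correlation 0.5.

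**1. The plan's own figure.** The design effect is 1 + 19 × 0.3 = 6.7. For unequal sizes, L = 20/(20 + 0.7/0.3) = 0.896, and relative efficiency is 1 − 1² × 0.896 × 0.104 = 0.906. The design effect becomes 6.7/0.906 = 7.39, which gives 90.8% power for 10 units and so reproduces the stated 90%. Also 320/0.67 = 478. The ICC of 0.3 is therefore the value on which the plan rests.

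**2. Closed form, equal hospitals of 20.** Hospital variance is 0.3 × 100 = 30. It splits into a constant part τ = 30*r* and a visit-specific part ω = 30(1 − *r*). Patient variance is 70, so 70/20 = 3.5 per hospital mean.

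- One visit: true variance τ + ω + 3.5 = 33.5; constant-intercept model about τ + ω/3 + 3.5.
- Difference between two visits: true variance 2ω + 2 × 70 × 0.5/20 = 2ω + 3.5; constant-intercept model 3.5.

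At *r* = 0.8, τ = 24 and ω = 6. The SE ratio (model/true) is √(29.5/33.5) = 0.94 at a visit and √(3.5/15.5) = 0.48 for the difference.

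| *r* | SE ratio, one visit | SE ratio, difference |
|---|---|---|
| 1 | 1.00 | 1.00 |
| 0.9 | √(31.5/33.5) = 0.97 | √(3.5/9.5) = 0.61 |
| 0.8 | 0.94 | 0.48 |
| 0.5 | √(23.5/33.5) = 0.84 | √(3.5/33.5) = 0.32 |

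**3. REML simulation, no true effect, planned model, *t* with 14 df.** Mean hospital size 20, size CV 0.5, complete data, no baseline covariate, 1000 replicates per scenario (Monte Carlo error about 0.7 points near 5%). Type I error at 6 months / 12 months / 12-minus-3-month contrast:

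| *r* | ICC 0.3 | ICC 0.1 |
|---|---|---|
| 1 | 4.7 / 5.5 / 3.1% | 4.6 / 4.7 / 3.1% |
| 0.9 | 6.9 / 5.8 / 19.0% | 5.1 / 5.2 / 6.5% |
| 0.8 | 7.6 / 6.8 / 29.2% | 6.1 / 5.8 / 11.7% |
| 0.5 | 10.2 / 9.8 / 42.8% | 9.0 / 7.4 / 22.9% |

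The simulated SE ratios at ICC 0.3 agree with step 2. For *r* = 0.9, 0.8 and 0.5 they are 0.97, 0.93 and 0.81 at 6/12 months, and 0.61, 0.49 and 0.36 for the contrast.

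**4. With the protocol's size CV of 1.** Two further simulations at ICC 0.3 used an average of 25 patients per hospital.

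- The first (400 patients, within-patient correlation 0.6, 600 replicates) gave 7% at 6/12 months and 43% for the contrast at *r* = 0.8. At *r* = 0.5 it gave 12–14% and 58%, with a mean 12-month SE of 2.44 against a true SD of 3.29 (ratio 0.74).
- The second (300 replicates) gave 6–9% at 6/12 months for *r* = 0.8–0.9 and 11–13% at 0.5. The contrast ranged from 32% to 62% over *r* = 0.9 to 0.5.

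**5. Adding a centre-by-visit random effect.** In step 3 the SE ratio returns to 0.995–1.03 wherever ICC 0.3 or 0.1 is combined with *r* below 1 (one contrast value at ICC 0.1 is 1.037), and type I error to 3.0–6.1%. In step 4 it is roughly 2–7%.

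**The case against.** **The error is conditional.** At *r* = 1 the planned model is calibrated, and no section gives *r*. This stands. A reader might infer that the trial's standard errors are too small as a matter of fact; the documents do not support that.

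**The largest figures concern a test the protocol does not name.** Section {20a} names visit-specific effects at 6 and 12 months, and the intervention-by-time term is what allows a mixed model to produce them. This also stands. A reader might infer that the trial plans a trajectory test with an error rate of 40% or more; it states no such test. The exposure arises only if the interaction or a between-visit difference is used to answer the objectives in Table 2.

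**Low correlations are less plausible than high ones.** Staff or service changes happen in calendar time. Enrolment is staggered from March 2021 to July 2023 (Trial status), so a hospital's 3-, 6- and 12-month visits cover overlapping periods. Assume uniform recruitment over 27.5 months and a hospital deviation that correlates only 0.5 with itself nine months later. The visit means then still correlate 0.98 (3 v 6 months), 0.94 (6 v 12) and 0.87 (3 v 12). GAS training is also described in {18a}. This makes values near 0.9 more credible than 0.5, although shorter recruitment at a site would lower them. At 0.9 the named results are nearly calibrated, but the contrast still rejects 19% or more at ICC 0.3.

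**The simulations simplify the plan.** They use complete data and no baseline covariate. They also use a planning ICC for GAS, although none is given for EQ-5D-5L or FI. The exact percentages are therefore indicative; at ICC 0.1 they are smaller.

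**The analysis plan may refine the model.** It may, but the hospital-level structure is stated here, so this changes a stated model and does not fill a gap.

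**Conclusion.** The point holds conditionally. The stated model assumes perfectly correlated hospital effects across visits, and its standard errors are too small if that fails. All figures rest on an assumed between-visit correlation.

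- **Named 6- and 12-month effects, ICC 0.3:** SE about 3–10% too small and type I error about 6–9% at correlation 0.8–0.9. At 0.5 the SE is about 19–26% too small (ratios 0.81 and 0.74) and the error 10–14%.
- **Any between-visit contrast, ICC 0.3:** type I error about 19–50% at correlation 0.8–0.9, depending mainly on how uneven the hospitals are.

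Only secondary outcomes are involved. The 3-month primary analysis is a separate regression with robust standard errors and is untouched. This is a cheap improvement. It matters most if the intervention-by-time term will be interpreted.

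**What to change.** In {20a}, and in the statistical analysis plan due before unblinding, replace the single centre intercept with random effects for study centre and for study centre by visit. Keep the unstructured within-patient matrix. Use a small-sample reference (Kenward-Roger, or *t* with 14 df) for the 6- and 12-month effects and for any intervention-by-time contrast.

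The cost is one sentence and one variance parameter. Intervals widen somewhat when hospital effects do drift, as they should. When they do not, the visit-specific SE barely changes (mean 2.92 against 2.91 in the 400-patient simulation). The contrast becomes slightly conservative (type I error 2.5% against 3.1% in step 3 at *r* = 1). With 16 hospitals the extra variance may be estimated at zero, in which case the random-effects structure reduces to the planned one.
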